### Secondary outcome measures

#### Spatiotemporal gait variables

Additional measures of walking stability will include stride length, stride time variability, double-limb support time, and gait velocity, when walking over an even and uneven surface. Our pilot study reported that wearing textured insoles for 2-weeks led to significant increases in mean stride length (right leg: 5.8 cm (*P* < 0.01); left leg: 4.4 cm (*P* < 0.01)), compared to baseline assessment [20]. Details of specific methods underpinning all measures are provided in the assessment section below.

#### Gait kinematics

During both even and uneven surface walking trials, lower limb gait kinematics will be collected using a 3D motion capture system and will include hip, knee and ankle joint angles (and their inter-relationships) and foot-to-floor angle to determine maximum toe clearance. Segmental measures of trunk inclination, as well as arm swing, mediolateral pelvis and head displacement will also be collected. Specific details are presented below.

#### Sensory measures

Light touch-pressure sensation will be determined by recording the smallest monofilament that the participant can perceive at five locations on the foot as detailed below [15]. Vibration sense will be measured using a digital stop watch, started when the tuning fork touches the participant’s skin at two sites on the feet, then stopped when the participant indicates the vibration can no longer be felt. The average of three trials will be recorded for both feet (seconds) [15]. For two-point discrimination, when the participant perceives two stimuli as one, the distance will be recorded in millimetres [15]. Ankle joint position sense will be determined by the participant performing the ankle joint position sense test [33].

#### Insole wear and falls

Participants will be followed for 12-weeks with insole wear self-reported diaries and falls calendars to determine (1) the number of hours insoles are worn and (2) the frequency, time, and location of any falls and injuries. In this study, a fall will be defined as an unexpected event in which the participant comes to rest on the ground, floor or lower level [34].

### Baseline assessments

Demographics, including sex, age, height, and body mass, will be collected. To characterise the study sample, participants will be asked to complete questionnaires that address relevant medical history and medications, length of time since diagnosis of MS, current MS symptoms using the MS Impact Scale (MSIS-29) [38], and perceived walking ability using the MS Walking Scale (MSWS-12) [39]. Quality of life, the impact of fatigue and pain, and perceived disability will be assessed using four self-report questionnaires: MS Quality of Life Instrument (MS QoL-54) [40]; Modified Fatigue Impact Scale (a questionnaire which measures how MS-related fatigue affects everyday life including physical, cognitive and psychosocial functioning [41]); Medical Outcomes Study (MOS) Pain Effects Scale (a MS-specific questionnaire which assesses how pain and disturbing sensations, such as burning or tingling, affect everyday life [42]); and the Perceived Deficits Questionnaire (a MS-specific questionnaire which assesses several domains of cognitive function that are commonly affected by MS, namely attention, retrospective memory, prospective memory, planning and organisation [43]). Number of self-reported falls experienced in the previous 12 months will be recorded, and current fear of falling assessed using the Falls Efficacy Scale-International [44].

Following the clinical screening examination, all participants will complete initial assessments of gait, foot sensation and proprioception (baseline assessment 1). Standing balance and activity levels will also be measured at baseline assessment 1 only. Each participant will receive a wireless activity monitor (activPAL, Glasgow, Scotland), to be worn every day for seven consecutive days, allowing us to characterise the activity of the study group, monitor habitual weekly activity levels and establish any relationships with gait performance at baseline. The increasing use of accelerometry in pwMS [45, 46] is accredited to its ability to allow monitoring of changes in walking impairments with disease progression (e.g. worsening of MS) or disease activity (e.g. acute relapse), over long periods of time [47]. Four weeks after baseline assessment 1, a second baseline assessment (baseline assessment 2) will be conducted. The purpose of this 4-week waiting period is to establish each participant’s natural rate of MS disease progression, specifically the magnitude of change in the primary and secondary outcome measures of gait, foot sensation and proprioception, prior to delivery of the intervention.

### Gait

Gait performance will be evaluated by completing a 12 m walk over an even surface and an uneven surface. The even surface will consist of a level, vinyl material: the top cover of an instrumented walkway (GAITRite^®^, CIR Systems, Inc., Havertown, PA 19083, USA). The GAITRite^®^ system is an electronic walkway, approximately 8.2 m long (the active area being 0.61 m wide and 7.32 m long), which has been shown to have high reliability [48, 49]. The uneven surface (placed directly on the laboratory floor, adjacent to the GAITRite^®^ walkway) will consist of two layers of thick soft foam, over which small blocks of wood of uneven shapes and sizes will be spread in a random manner, with a top layer of artificial grass covering the walkway, using previously described methods [50]. Maintenance of stability when walking requires individuals to control their centre of mass within a constantly changing base of support; this becomes even more challenging when the surface is uneven, increasing the risk of loss of balance, resulting in a fall. Deficits in balance control during walking or, conversely, the therapeutic benefit of interventions (such as shoe insoles) on walking performance may only become apparent when the balance challenge is sufficiently demanding. The uneven walking surface will emulate a situation encountered in daily life. A start and finish line will be marked on the floor 2 m in front and 2 m behind both the even and uneven surface walkways, allowing participants to accelerate and decelerate outside the walkways [48]. Participants will be positioned at the start line and instructed to walk at their comfortable, self-selected walking pace. Five walking trials will be completed on the even surface and five trials on the uneven surface, each whilst barefoot, wearing standardised footwear only, and wearing two different shoe insoles (textured and smooth) within standardised footwear. The test sequence (footwear condition, surface) will be randomised. Spatiotemporal gait variables will be measured using the GAITRite^®^ system (sampling rate 80 Hz) when walking over the even surface, and using an 11-camera Vicon^®^ motion capture system (Vicon, 6 × MX13 and 5 × T40 cameras, giganet control box, with a MX Net and Mx Link), sampled at 200 Hz, when walking over the uneven surface. Participants will have multiple reflective markers attached to their body, following the Vicon PlugIn Gait full body model. The Vicon system records the position of reflective markers placed at standardised anatomical sites on the upper and lower body and will be used to measure spatiotemporal gait variables and gait kinematics.

### Balance

Standing balance will be assessed to provide a measure of basic, unperturbed postural stability. Participants will stand on an AMTI force platform (sampling rate 1000 Hz), using a standardised foot position (heels placed 1/10th participants height apart and angled to 14° [51]), and arms hanging by their sides, for 30 seconds [52]. Double-limb standing tests will be performed on a firm and foam surface, with their eyes open and eyes closed. To prevent vestibular disruption when standing with eyes open, participants will be instructed to look straight ahead and focus on the middle of a black circular visual target (10 cm diameter), mounted onto a board positioned 3 m from the centre of the force platform, and adjusted to the eye level of each participant. Standing balance will be assessed whilst barefoot, wearing standardised footwear only, and when wearing two different shoe insoles (textured and smooth) within standardised footwear. The test sequence (footwear condition, surface, vision) will be randomly presented. Measures of baseline standing balance will include centre of pressure path velocity, range and standard deviation of centre of pressure movement in the anterior-posterior and ML directions.

### Foot sensation and proprioception

Somatosensory function, including light touch-pressure sensation, vibration sense, and two-point discrimination, will be assessed. Semmes-Weinstein monofilaments (smallest (1.65) to largest (6.65)) will be used to determine light touch-pressure sensation at five locations on the foot, namely the plantar surface of the great toe, first metatarsal head, fifth metatarsal head, heel, and dorsum of the foot between the first and second toes [53]. The monofilaments will be applied perpendicular to the skin for 1.5 seconds, and the participant will be required to indicate whether the fibre can be felt. The smallest monofilaments (1.65–4.08) will be applied three times consecutively, whilst larger ones (4.17–6.65) will be applied only once [15]. Duration of vibration sense will be measured using a 128-Hz frequency tuning fork at the first metatarsal head and medial malleoli of both feet [15]. The ability to distinguish between two light-touch stimuli (two-point discrimination) will be measured using an aesthesiometer applied to the skin at three foot regions: tip of the great toe, first to second metatarsal interspace, and fifth metatarsal head. Each region will be touched with either one or two points simultaneously in a random order, with approximately 2 seconds between each application of the stimuli. Assessment will begin with the two stimuli at the maximum distance apart, and decrease until the participant can no longer differentiate the two points [15]. Foot position awareness will be assessed bilaterally using the ankle joint angle reproduction test [33]. The investigator will passively set the participant’s ankle joint to three pre-determined angles in plantarflexion and dorsiflexion directions, relative to a neutral foot position. A variable time and trajectory will be used when positioning the foot in order to eliminate extraneous cues and psychophysical processes. The participant will be asked to reposition the ankle joint at the target angle by moving only the foot segment. Accuracy in joint positioning will be determined by measuring the difference between the target and actual angles using an internet-based goniometer [54]. This application has been shown to be a valid method for measuring joint angles and has a high level of inter-rater (ICC2,1 = 0.96 to > 0.99) and intra-rater (ICC = all > 0.99) reliability [54].

### Post-intervention assessment

Gait, foot sensation and proprioception will be assessed within 2 weeks of the end of the 12-week intervention period, using the same procedures employed at baseline. A 12-week intervention period will provide maximal time to allow for the accrual of any sensory training effects and accumulation of meaningful changes in outcome measures, in particular for participants with MS who show minimal gait disturbance at baseline and currently engage in an active lifestyle. This intervention period is consistent with previous randomised controlled trial intervention studies conducted in pwMS [11, 27, 28], and footwear intervention trials [55, 56]. This final point of assessment will (1) quantify whether any immediate changes in gait, observed at baseline, have accrued over time, or if additional effects can be seen and (2) determine whether there are any alterations in the perception of foot sensation or proprioception, which may suggest the insoles have a sensory training effect. Participants will be asked to return their insole wear diaries and falls calendars at this time. Participants will also be asked to rate the level of comfort experienced when wearing the insoles by way of a series of 100 mm visual analogue scales used in previously published research [57].

### Data analysis

All analyses will be conducted in a blinded manner, on an intention-to-treat basis, with the alpha set to 0.05. We will explore frequency distributions, percentages and calculate means and standard deviations for the outcome measures. Differences between intervention and control groups in spatiotemporal gait variables, gait kinematics, foot sensation or proprioception, over the intervention period, will be explored using General Linear Models (repeated measures analysis of variance, ANCOVA), in a two group (smooth control insole; textured insole) by three phase (baseline assessment 1, baseline assessment 2, post-intervention) model. We will adjust for potential confounding variables (e.g. age, sex, disease duration) by using these as covariates. Non-parametric tests will be used where data is not normally distributed or violates the assumption of sphericity. Multiple regression modelling will be used to determine any relationships between foot sensation, proprioception and measures of gait performance. Data will be analysed using SPSS version 22 (SPSS Inc., Chicago, IL 60606, USA).

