### Sample size

Sample size has been calculated for the primary outcome measure, ML base of support during even surface walking, based on our pilot data [20]. Our preliminary study reported mean (SD) readings at baseline for base of support of 13.78 (5.11) cm and a significant mean change of –1.66 cm (*P* = 0.02) at 2-weeks post intervention. With a power of 80 %, and alpha level of 0.05, a calculation for two related groups indicated that 76 participants were required in each group. In our pilot study, we recruited 46 pwMS, with no loss to follow-up across two visits (although completion of all test procedures was limited by fatigue in some participants). As this randomised controlled trial involves a longer intervention period, we will allow for a 15 % attrition rate. An 85 % retention rate over a 16-week period (baseline assessments at week 0 and week 4, intervention 12-weeks, post-intervention assessment at week 16) is appropriate based on previous MS intervention studies. Three randomised controlled trials with 12-week intervention periods conducted in pwMS, report retention rates of 82 % [27], 88 % [11], and 90 % [28]. Therefore, 88 participants per group will be recruited, giving a total of 176 participants.

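### As written, the three-phase General Linear Model analyses only participants with complete data, which conflicts with the stated intention-to-treat basis; a mixed model with a sensitivity analysis should replace it

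*Protocol article*

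**What the plan says.** The Data analysis section of the protocol article sets the analysis set: "All analyses will be conducted in a blinded manner, on an intention-to-treat basis, with the alpha set to 0.05". It then says that differences between the groups "will be explored using General Linear Models (repeated measures analysis of variance, ANCOVA"), with the two insole groups crossed with three phases: baseline assessment 1, baseline assessment 2 and post-intervention. Covariates such as age, sex and disease duration are to be added, and "Data will be analysed using SPSS version 22". The section gives no imputation and no other rule for a missing visit or covariate.

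Four other sections bear on this:

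- **Sample size** allows for 15% attrition over 16 weeks and cites retention of 82%, 88% and 90% in three earlier trials. It reports that the pilot lost nobody to follow-up but that "completion of all test procedures was limited by fatigue in some participants".
- **Randomisation and blinding** places allocation after baseline assessment 2.
- **Background** (last paragraph) defines the primary aim as change from baseline assessment 2 to post-intervention.
- **Participants** removes from the study enrolled participants whose symptoms flare for more than 24 hours in the 4 weeks before the intervention period or during it.

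**The concern.** A classical repeated-measures ANOVA fitted through a General Linear Model needs one complete row per person. Anyone lacking one phase or one covariate is deleted from the whole analysis, not just from the missing cell. The named method therefore decides what happens to incomplete cases, and its decision differs from what the intention-to-treat label promises.

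Two consequences follow. The first is waste. Baseline 1 is not part of the primary contrast, yet a missing baseline 1 value removes someone whose baseline 2 and post-intervention values were both observed. The second is possible bias. If the people lost differ between arms in ways related to their gait, the difference among completers need not equal the difference among all those randomised. Fatigue and worsening MS are plausible reasons for incomplete data in this population.

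**Working it through.** **1. The protocol's own sample size.** Inputs from Sample size: "mean (SD) readings at baseline for base of support of 13.78 (5.11) cm" and "a significant mean change of –1.66 cm", and then "With a power of 80 %, and alpha level of 0.05, a calculation for two related groups indicated that 76 participants were required in each group". The paired formula is n = (SD × (z₀.₉₇₅ + z₀.₈₀) / δ)².

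- (5.11 × (1.960 + 0.842) / 1.66)² = 74.4, so 75; the paired t version gives 76.3. The stated 76 is reproduced.
- 76 × 1.15 = 87.4, so 88 as stated. Dividing instead, 76 / 0.85 = 89.4, so 90.
- With 88 recruited, 76 remain only if the loss is at most 1 − 76/88 = 13.6%.

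**2. Completers at the protocol's own rates.** Completers per arm = 88 × retention. Power uses the same paired t formula.

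| Retention | Completers per arm | Lost of 176 | Power, protocol's paired formula |
|---|---|---|---|
| 82% (cited trial) | 72.2 | 31.7 | 77.7% |
| 85% (planned) | 74.8 | 26.4 | 79.2% |
| 88% (cited trial) | 77.4 | 21.1 | 80.6% |
| 90% (cited trial) | 79.2 | 17.6 | 81.5% |

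The power column only shows scale. Whether a paired calculation suits a comparison of two independent groups is a separate matter.

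**3. Loss from unfinished test blocks.** The Gait section asks for 5 trials × 2 surfaces × 4 footwear conditions = 40 walks of 12 m at each assessment, in randomised order, from people who need only be able to walk 100 m. Baseline 1 also carries the standing-balance tests. The documents give no rate for unfinished blocks, so the following is an assumption shown as a range. On top of 15% attrition, let a share p of those retained lack the primary condition. If the same people are affected at every visit, 0.85 × (1 − p) remain. If the visits are independent, 0.85 × (1 − p)³ remain.

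| Assumed p | Same people each visit: share left, per arm | Independent visits: share left, per arm |
|---|---|---|
| 2% | 83.3%, 73 | 80.0%, 70 |
| 5% | 80.8%, 71 | 72.9%, 64 |
| 10% | 76.5%, 67 | 62.0%, 55 |

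Fatigue probably recurs in the same people, so the left column is the more likely guide.

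**4. Possible bias.** If the group difference in unobserved outcomes departs from that in observed outcomes by g cm, and 15% are missing equally in both arms, the estimate is off by 0.15 × g. For assumed g of 0.5, 1 and 2 cm this is 0.075, 0.15 and 0.30 cm, or 4.5%, 9% and 18% of 1.66 cm. The documents give no value for g; 2 cm exceeds the planned effect itself and is an extreme case.

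**5. Which visit is lost.** Allocation follows baseline 2, so a randomised participant will normally have attended both baselines. Loss after randomisation is then mainly the single post-intervention visit, plus blocks left incomplete at visits that were attended.

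**The case against.** The strongest reply is that this rests on silence. The article is a condensed account, it never says complete-case, and a full protocol or analysis plan may impute before fitting. That limits the point to the plan as written. It does not remove it, because the article does more than leave missing data open: it names a specific model whose handling of incomplete cases is known.

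A reader might infer that at least 15% of randomised participants will be discarded. The documents do not support that. The 15% is a planning allowance, two of the three cited trials lost less, and the 16 weeks include the 4 weeks before allocation. People lost in that month are never randomised and fall outside an intention-to-treat set.

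A reader might also infer that the result must be biased because dropout relates to gait. That is too strong. Dropout related to baseline gait but similar in both arms does not bias the difference unless the insole effect also varies with baseline gait. No section shows differential dropout, and the pilot remark does not say that base of support was among the unfinished measures.

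Finally, a mixed model gains little for someone who misses the only post-intervention visit, since that person contributes baseline data alone. This stands. The gain lies with people who have partial baseline data and in a weaker missing-data assumption; outcome-related dropout needs the sensitivity analysis.

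**Conclusion.** The concern holds for the plan as written: the named model analyses completers, and that conflicts with the intention-to-treat statement in the same section. On the protocol's own figures about 15% could be lost (10% to 18% across the cited trials), leaving roughly 72 to 79 of 88 per arm, with part of the loss possibly before randomisation. Unfinished test blocks add an unquantified number, some with the primary contrast fully observed. The rates in step 3 and the biases in step 4 are illustrations under stated assumptions, not forecasts. The conclusion assumes that no unseen document adds imputation.

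The exclusion for exacerbation in the Participants section is a second conflict with intention-to-treat. Its expected frequency is not given, and a mixed model does not resolve it if those participants' data are removed.

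**What to change.** - **Primary analysis.** Replace the repeated-measures General Linear Model with a likelihood-based linear mixed model (MIXED in SPSS). Use all available visits of every randomised participant, an unstructured covariance over the three phases, and no group effect at the two baselines, which both precede allocation. The group difference at post-intervention is the primary estimate. With complete data this is close to a baseline-adjusted ANCOVA. Since MIXED also drops records with missing covariates, use only covariates collected on everyone at entry, or state how gaps are filled.
- **Sensitivity analysis.** The mixed model relies on data missing at random, so add one analysis in which missing textured-arm outcomes are imputed from the smooth arm.
- **Consistency.** Reconcile the exclusion of enrolled participants with exacerbations (Participants) with the intention-to-treat statement (Data analysis), so that it is clear whether their data remain in the analysis set.

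The cost is revised analysis wording and slightly more programming. Sample size, visits and procedures need not change for the modelling part.

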This randomised controlled trial will determine whether wearing textured shoe insoles for 12-weeks can improve gait when walking over even and uneven surfaces in pwMS. The primary aim of this study is to explore whether prolonged wear of textured insoles alters ML base of support (as a measure of walking stability) from baseline assessment 2 to the post-intervention assessment. Secondary aims are to explore whether prolonged wear of textured insoles alters other spatiotemporal gait parameters including stride length, stride time variability, double-limb support time and gait velocity, gait kinematics (specifically lower limb joint and trunk movement), and changes in the perception of foot sensation or proprioception, as underlying mechanisms associated with improvements in spatiotemporal gait parameters.

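### The two-group by three-phase model treats two pre-randomisation visits as outcome levels and names no single test for the primary aim

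*Protocol article*

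**What the plan says.** - **Aim.** The last paragraph of the Background sets the primary aim as the change in mediolateral (ML) base of support "from baseline assessment 2 to the post-intervention assessment".
- **Timing.** Under Randomisation and blinding, envelopes are opened after baseline assessment 2. Both baseline assessments therefore precede allocation.
- **Model.** Data analysis plans general linear models, labelled as repeated-measures analysis of variance and ANCOVA, "in a two group (smooth control insole; textured insole) by three phase (baseline assessment 1, baseline assessment 2, post-intervention) model". It does not say which term of the model is the primary test.
- **Covariates.** "We will adjust for potential confounding variables (e.g. age, sex, disease duration) by using these as covariates". The earlier values of the outcome are not among the examples; they are levels of the repeated factor.
- **Second baseline.** Baseline assessments explains the four-week wait as a way to "establish each participant’s natural rate of MS disease progression", meaning the change in the outcomes before the intervention.

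**The concern.** In a randomised trial the treatment can affect only what is measured after allocation. Here that is one of the three phases. The stated model has two omnibus terms that involve group, and neither isolates the aim.

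- **Group by phase (2 df)** asks whether the between-group difference varies in any way across the three visits. One of its two components is a group difference in change from baseline 1 to baseline 2. Randomisation makes that component pure chance, yet it can contribute to a significant result.
- **Group main effect (1 df)** averages the group difference over all three visits. Two of these carry no treatment effect, so it targets one third of the effect.

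What is at stake is first interpretation: a significant interaction would not by itself show a treatment effect at 12 weeks, and the text commits to no single estimate as the trial's answer. Power comes second, because a degree of freedom is spent on a comparison of no interest.

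**Working it through.** **Inputs from the Sample size section.** "With a power of 80 %, and alpha level of 0.05" (taken as two-sided, since the sidedness is not stated); "readings at baseline for base of support of 13.78 (5.11) cm"; "a significant mean change of –1.66 cm", used here as the between-group difference δ = 1.66 cm with σ = 5.11 cm.

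**The plan's own figure.** The section states: "alpha level of 0.05, a calculation for two related groups indicated that 76 participants were required in each group". A paired formula gives n = (1.960 + 0.842)² × (5.11/1.66)² = 7.849 × 9.476 = 74.4, so 75. The exact paired t calculation gives 77. The stated 76 is thus reproduced as a paired calculation. Attrition: 76 × 1.15 = 87.4, so 88 recruited. With 15% lost, 88 × 0.85 = 74.8, so n = 75 per arm is used below.

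**Assumption.** The documents report no between-visit correlation ρ. I take it as equal for all pairs of visits and show 0.5 to 0.9. The effect is present at post-intervention only.

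**Formulas** (λ is the noncentrality parameter)

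- Group by phase: F with 2 and 2(2n − 2) = 296 df; λ = nδ² / [3σ²(1 − ρ)].
- ANCOVA on both baselines: F with 1 and 2n − 4 = 146 df; λ = (n/2)δ² / [σ²(1 − 2ρ²/(1 + ρ))].
- Group main effect: F with 1 and 148 df; difference δ/3 = 0.553 cm; variance of a person's mean σ²(1 + 2ρ)/3.
- Change from baseline 2: F with 1 and 148 df; variance of a change 2σ²(1 − ρ).
- Single contrast, post minus mean of the two baselines: same λ as group by phase, but 1 and 148 df.

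**Example at ρ = 0.7.** Group by phase: λ = 75 × 2.7556 / (3 × 26.112 × 0.3) = 8.79, power 75.6%. ANCOVA: λ = 37.5 × 2.7556 / (26.112 × 0.4235) = 9.34, power 85.9%.

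**Power (%), 75 per arm**

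| ρ | Group by phase | ANCOVA, both baselines | Gap (points) | Post minus mean baseline | Change from baseline 2 | Group main effect |
|---|---|---|---|---|---|---|
| 0.5 | 52.2 | 67.7 | 15.5 | 62.6 | 50.7 | 12.7 |
| 0.6 | 62.3 | 76.0 | 13.7 | 72.3 | 59.9 | 12.0 |
| 0.7 | 75.6 | 85.9 | 10.3 | 83.8 | 72.3 | 11.4 |
| 0.8 | 90.9 | 95.7 | 4.8 | 95.0 | 87.8 | 10.9 |
| 0.9 | 99.7 | 99.9 | 0.2 | 99.9 | 99.3 | 10.5 |

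**Where the loss comes from.** The single contrast has the same λ as the group-by-phase test, so the whole difference between those two columns is 2 df against 1. At ρ = 0.7 that accounts for 83.8 − 75.6 = 8.2 of the 10.3 points. The move from the contrast to ANCOVA adds the other 2.1.

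**Unequal correlations.** In simulations with 76 per arm and the Greenhouse-Geisser correction, three patterns of unequal correlation gave gaps of 9.7 to 11.1 points.

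**The case against.** The strongest defence is that the stated model is valid and can deliver the aim. Much of it stands.

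- **Type I error.** A reader might infer that the baseline component inflates false positives. It does not. With no treatment effect, randomisation makes both components of the interaction null, so the test keeps its 5% level. The fault is in what a significant result means.
- **Main effect.** A reader might take the 11–13% power as the trial's power. Nothing in the protocol names the main effect as the treatment test, and the wording about differences over the intervention period points to group by phase. The low figure applies only if the main effect is read as the treatment test.
- **Estimates.** A follow-up contrast with an interval can be drawn from the same model, and the text does not exclude one. A single contrast recovers most of the lost power.
- **Power and the aim.** A reader might infer that the loss arises from departing from the stated aim. The simple change from baseline 2 in fact has slightly less power than the group-by-phase test (72.3% against 75.6% at ρ = 0.7). The gap is measured against a better analysis of the same data.
- **Covariates.** The list is given as examples and is not closed, and the baseline values already enter the model as outcome levels. It would be too strong to say that baseline information is ignored.
- **Second baseline.** A reader might object that two visits cannot give an individual progression rate. No planned analysis uses individual rates, so this is a side issue.

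What the defence does not remove is that the model the article fixes has two of its three outcome levels before randomisation and no term designated to answer the primary aim. That is a mismatch in what is written, not detail left to an analysis plan.

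**Conclusion.** The point holds as one of target and interpretation first and of power second. Neither omnibus term that involves group isolates the primary aim, and a significant group-by-phase result need not reflect treatment.

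The power cost depends on a correlation that the documents do not give. Under equal correlation, 75 per arm, a 1.66 cm difference and SD 5.11 cm, it is about 15 points at 0.5, 10 at 0.7, 5 at 0.8 and almost none at 0.9. A reader might want one figure, such as a loss of 10 to 14 points. At these planning values that range holds only for correlations of roughly 0.6 to 0.7, so it cannot be stated as fact. ANCOVA on both baselines had the higher power at every correlation tried.

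Because type I error is preserved and the needed contrast can be obtained from the stated model, the severity is SHOULD-FIX.

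**What to change.** In Data analysis, name one primary test: a 1-df ANCOVA of post-intervention ML base of support on group, adjusted for the baseline 1 and baseline 2 values of the same measure (or their mean) and for the planned age, sex and disease duration. A mixed model with the group means constrained equal at both baselines is an equivalent choice. Report the adjusted mean difference with its 95% CI. Use the baseline 1 to baseline 2 change descriptively only; the concurrent control group already accounts for natural change.

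The cost is a change of analysis wording. The data are already to be collected at the planned visits, and no visit, measurement or participant is added.
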